**Figure 4 figure4:**
[figure not shown]
Pairwise comparison of data obtained during AMASIA (imp**A**ct of **M**ayzent [siponimod] on second**A**ry progressive multiple **S**clerosis patients in a long-term non-**I**nterventional study in Germ**A**ny) and PANGAEA 2.0 EVOLUTION, including study design, patient characteristics, and concordant and additional measures of multiple sclerosis (MS) activity, disability progression, functional domains, quality of life, and socioeconomic factors. Standard of care includes current disease-modifying therapy or no treatment at inclusion. CGI: clinical global impression; EDSS: Expanded Disability Status Scale; FSMC: Fatigue Scale For Motor And Cognitive Functions; MRI: magnetic resonance imaging; MS-AS: MS activity scale score; MS-HRS: Multiple Sclerosis Health Resource Utilization Survey; RRMS: relapsing remitting multiple sclerosis; SDMT: Symbol Digit Modalities Test; SPMS: secondary progressive multiple sclerosis; UKNDS: United Kingdom Neurological Disability Scale.

### Data Collection and Management Using the Multiple Sclerosis Documentation System MSDS3D

Data will be recorded exclusively online by the physician responsible, using the electronic case report form in the MS documentation system MSDS3D [62,63]. The MSDS3D software combines data documentation with patient management. It now has expanded safety management with regard to the characteristics of different treatments and populations [64,65]. Data will be computerized in a pseudonymous form, and all entries will be automatically controlled for plausibility at the time of data entry and reviewed daily by the database coordinator. Data management processes including data analyses will be conducted by the data management team of the responsible clinical research organization (Winicker Norimed GmbH Medical Research).

### Statistical Analysis

For analysis, descriptive statistics will be primarily used. The full analysis set includes all patients receiving at least one dose of siponimod with at least one available post-dose data recording. Sample statistics such as median, mean (SD), minimum, maximum, 5% percentile, 1st quartile, 3rd quartile, 95% percentile, and number of valid and missing values will be presented in tabular form. Distributions of absolute and relative frequencies will be reported for nominal and ordinal-level data. Incidence rates of all safety outcomes (events per patient-year) will be evaluated for the patient population included. A propensity score matching adjustment, possibly using a caliper-based nearest-neighbor approach as seen in Alsop et al [66], will be used to compare data from AMASIA with data from the PANGAE 2.0 EVOLUTION arm. Possible predictive baseline and prestudy variables to be included in the model are as follows: age at baseline (years), sex, time since diagnosis at baseline (years), treatment at baseline, number of relapses in the past 12 months before baseline, and EDSS score at baseline. A multivariable logistic regression model will be fitted with the treatment arm as the dependent variable. The distribution of propensity scores before and after matching will be analyzed. Using the Medical Dictionary for Regulatory Activities, AEs are categorized according to system organ class and preferred term for individual adverse events (for AEs, serious AEs, adverse drug reactions, serious adverse drug reactions). For all analyses, SAS version 9.2 will be used.

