## Methods

### Study Design

AMASIA is a multicentric, open-label, prospective NIS on adult SPMS patients with active disease as evidenced by relapses or MRI features of inflammatory activity. Clinical diagnosis and decision for siponimod therapy will exclusively be made by the treating physician prior to enrollment and according to clinical routine practice and drug label information [34] to ensure real-world conditions.

Both disability progression, as assessed by an increase in Expanded Disability Status Scale (EDSS) scores, and decline of cognitive processing speed are important indicators of disease burden in MS [35-37]. Therefore, in AMASIA, a novel functional composite primary endpoint combining the 6-month confirmed disease progression (6M-CDP) of the EDSS score and SDMT score is utilized. This composite endpoint has been validated in Germany [38] and will be analyzed after 36 months of siponimod therapy to assess long-term effects of siponimod under real-world conditions. This combined 6M-CDP has been successfully applied for the evaluation of EXPAND patients to increase the sensitivity for SPMS progression of both single measures [38,39]. Confirmed disability progression on EDSS is defined as ≥1.0-point worsening in patients with baseline scores ≤5.0 or 0.5-point worsening in patients with baseline scores >5.0. Concomitantly, a ≥4.0-point SDMT worsening from baseline is considered as clinically relevant [40].

To further evaluate the long-term benefits from siponimod treatment in clinical routine, changes in EDSS (after 36 months) and quality of life scores as well as data on safety and long-term adherence (treatment discontinuation and interruption) will be assessed as secondary endpoints. Adherence will be evaluated on the basis of duration of siponimod intake as well as frequency of discontinuation and dose retitration per patient-year. Additional secondary endpoints are exploratory in nature and concern socioeconomic aspects [41], the characteristics of patients receiving their first dose of siponimod, the timing of therapy initiation, and its impact on disease progression. Furthermore, the utility of progression questionnaires (aligned with the online tool MSProDiscuss) and mobile/digital apps for MS monitoring will be documented [42].

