#### Observational Phase

Assessments during the 3-year observational period are depicted in Figure 3. Data on clinical examinations and MS disease status are obtained quarterly, if available. Data on MS disease status include MRI findings concerning number and volume of T2 hyperintense lesions, Gd-enhancing lesions, T1 hypointense lesions, and brain volume changes as well as EDSS and MS activity scale scores. The latter documents time, duration, intensity, treatment, and recovery of relapses.

Results of functional tests and questionnaires are obtained every 6 months (except for the questionnaire on the quality of life of caregivers [51]). Functional tests comprise the SDMT [36], timed 25-foot walk [52,53], and the nine-hole peg test [54] to assess neurological dysfunction and disability of lower and upper extremities. Furthermore, different questionnaires address the patients’ [55-58], physicians’ [59,60], and relatives’ perspectives as well as socioeconomic aspects [61]. Disease progression will be additionally judged by means of a progression questionnaire aligned with the online tool MSProDiscuss, which is intended to facilitate the discussion between physicians and patients about SPMS [42,60].

Occurrence, duration, causal relationship to therapy, counteractive measures to and outcomes of AEs, and treatment discontinuation and interruption will be documented throughout the study. AEs are defined as any unfavorable change in the patients’ pretreatment condition, regardless of their potential relation to treatment and irrespective of whether medication was taken as intended. Serious AEs comprise lethal or life-threatening events leading to persistent or significant disability, congenital anomaly or birth, hospitalizations, and other medically significant events that compromise the safety of patients.

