## Discussion

Here, we report the study design of AMASIA, a NIS prospectively including 1500 SPMS patients to be treated with siponimod in the clinical routine of up to 250 German neurological centers. This study will provide first insights on the benefit of siponimod treatment in clinical routine. During the 3-year observational phase, the long-term effectiveness and safety of siponimod will be assessed under real-world conditions, along with data on the quality of life of both patients and caregivers as well as socioeconomic aspects. Overall, the study aims at obtaining a detailed real-world safety and benefit profile of siponimod, complementing both the phase-III study data of EXPAND [29] and the NIS data of PANGAEA 2.0 EVOLUTION [9] (Figure 1).

The primary endpoint of the study is the 6-month confirmed progression of both disability worsening and cognitive decline, as assessed by a novel composite endpoint comprising 6M-CDP in EDSS and SDMT [38]. In clinical trials, EDSS is the most common outcome measure to determine disability progression in MS and a widely used inclusion criterion to define study populations [67]. However, EDSS alone suffers from limited sensitivity, as it is restricted in assessing impairments of upper extremities and cognition, especially at higher scores [68,69]. Since cognition is more severely and more frequently affected in SPMS patients than in RRMS and even primary progressive MS patients [70-72], the SDMT, indexing the most frequently affected information processing speed domain, was chosen as an additional primary outcome measure. In the assessment of information processing speed, SDMT has been proven to be superior to other tests such as the Paced Auditory Serial Addition Test. Moreover, it is simple and requires less time and assessor expertise to complete [73], and several trials have demonstrated its sensitivity in the evaluation of treatment effects [30,74]. Since Kappos et al [38] showed that 6M-CDP, as assessed by either EDSS or SDMT, is of limited sensitivity when compared to the combined 6M-CDP considering both, we decided to employ this novel composite endpoint to increase sensitivity for changes and therapeutic effects of siponimod.

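### The candidate propensity covariates omit baseline SDMT and pre-baseline MRI activity, and the one matching diagnostic named cannot show imbalance on either

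*Protocol article*

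**What the plan says.** The Statistical Analysis section of the Protocol article describes the comparison tentatively: "A propensity score matching adjustment, possibly using a caliper-based nearest-neighbor approach". The score comes from a logistic regression with treatment arm as the dependent variable. The candidate covariates are introduced with "Possible predictive baseline and prestudy variables to be included in the model are as follows: age at baseline (years), sex, time since diagnosis" and end with "treatment at baseline, number of relapses in the past 12 months before baseline, and EDSS score at baseline". One diagnostic is named: "The distribution of propensity scores before and after matching will be analyzed".

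The Study Design section defines the primary endpoint as "a novel functional composite primary endpoint combining the 6-month confirmed disease progression (6M-CDP) of the EDSS score and SDMT score is utilized". For the cognitive component, "a ≥4.0-point SDMT worsening from baseline is considered as clinically relevant". The same section limits AMASIA to SPMS that is active, shown either by relapses or by MRI.

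The section on the matched comparison gives EVOLUTION's entry criteria: age 18 to 65 years, EDSS 3.0 to 6.5, a previous RRMS diagnosis, a current diagnosis of SPMS or of RRMS at risk for SPMS, and treatment status. It states no activity criterion. It lists cognition among the outcomes to be compared.

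**The concern.** A propensity score can balance only the variables in its model and whatever is correlated with them. The list covers one component of the composite (EDSS) but not the other (SDMT). It covers one route to active disease (relapses) but not the other (MRI). EDSS is a weak stand-in for SDMT by the article's own account: the Discussion gives the poor coverage of cognition by EDSS as a reason for adding SDMT to the endpoint.

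The Discussion says comparability of the two studies is ensured, and offers the matched comparison as the answer to the lack of randomisation. If the matched sets differ on baseline cognition or recent MRI activity, and those variables are related to progression, the difference between arms mixes treatment with baseline state, and the named diagnostic would not show it.

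**Working it through.** **The plan's own figures.** The Sample Size section uses p = 0.622 and 1000 completers. With a 95% two-sided interval (assumed, since no level is stated), the half-width is 1.96 × √(0.622 × 0.378 / 1000) = 0.0301, which agrees with the stated 3.0%. With 13% annual dropout over 3 years, 1000 / 0.87³ = 1519, against 1500 planned (1500 × 0.87³ = 988). These figures size a single-arm proportion. The covariate list does not enter them.

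**Roles of the variables set side by side.**

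| Baseline variable | Role in AMASIA | In the candidate list? |
|---|---|---|
| EDSS | Component of the composite | Yes |
| SDMT | Component of the composite; worsening counted from baseline | No |
| Relapses | First route to active disease | Yes, 12-month count |
| MRI activity | Second route to active disease | No |

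An AMASIA patient who qualifies on MRI alone may have a relapse count of zero. On the six listed variables that patient can look the same as an EVOLUTION patient with no relapses and no active lesions. Nothing in the stated model separates them.

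**What the score distribution can show.** The score is a function of the listed covariates only. Agreement of the scores is informative about an unlisted variable only as far as that variable is correlated with listed ones.

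**Illustration by simulation.** Every input here is an assumption, not a figure from the documents: 1000 patients per arm; no true treatment effect; five listed-type covariates, two of them shifted by 0.2 SD between arms; one omitted variable correlated 0.4 with EDSS; 1:1 nearest-neighbour matching with a caliper of 0.2 SD of the logit score; 30 replicates per setting.

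| Shift in omitted variable (SD) | Its SMD after matching | False difference in points, at OR 1.3 / 1.5 / 2.0 per SD |
|---|---|---|
| 0.2 | 0.11 | 0.4 / 0.8 / 1.6 |
| 0.3 | 0.21 | 0.9 / 1.6 / 3.0 |
| 0.5 | 0.41 | 2.2 / 3.8 / 5.8 |

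Throughout, the SMD of the matched score was 0.003 and the largest SMD on a listed covariate was about 0.02, so the match looked excellent. With the variable in the model, its SMD fell to 0.006 or less and the false difference to within 0.3 points.

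The Monte Carlo standard error is about √(2 × 0.235 / 872) / √30 = 0.004, or 0.4 points, where 0.235 = 0.378 × 0.622 and 872 is the mean number of pairs. The smallest entries are therefore imprecise. A first-order check, SMD × ln(OR) × p(1 − p), gives 0.112 × 0.262 × 0.235 = 0.7 points at the low end and 0.409 × 0.693 × 0.235 = 6.7 at the high end. It ignores attenuation over the other risk factors, so it runs somewhat above the simulated values.

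**A second illustration by odds.** Take a comparator progression rate of 100 − 52.3 = 47.7% (EXPAND placebo), odds 0.477 / 0.523 = 0.912. Assume a residual imbalance of 0.2 to 0.4 SD and a log-odds of 0.3 to 0.5 per SD.

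- Low end, exp(0.2 × 0.3) = 1.06: 49.2% if the comparator is the worse group at baseline, 46.2% if it is the better one, a shift of about 1.5 points.
- High end, exp(0.4 × 0.5) = 1.22: 52.7% or 42.7%, a shift of about 5 points.

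For scale, the siponimod–placebo difference quoted from EXPAND is 62.2 − 52.3 = 9.9 points. The article states no expected AMASIA–EVOLUTION difference.

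**The case against.** The strongest reply is that nothing here is final. The list is headed as possible variables, the matching method is tentative, and this is a condensed article whose full analysis plan may add covariates and a balance table. That stands in part. A reader might infer that the score distribution will be the only check, but the text says only that it will be analysed and excludes nothing. The omissions from the list are different: the article chose to name candidates, and the named set leaves out a component of its own endpoint and one of its own entry routes.

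A reader might also infer that imbalance on cognition is to be expected because EVOLUTION enrols RRMS patients and "cognition is more severely and more frequently affected in SPMS patients than in RRMS". The documents do not support this. The Introduction and the limitations paragraph of the Discussion both describe the matched comparison as one between SPMS patients on siponimod and SPMS patients on standard care, so RRMS patients may never enter the matched set. If they did, the comparator would tend to have better cognition, and under the assumed risk gradient the bias would run against siponimod. The MRI argument does not depend on this.

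Other limits also stand. No passage ranks SDMT or MRI activity as predictors of progression. The composite is not expressly named as the outcome of the matched comparison, though cognition is. The 12-month relapse count captures part of inflammatory activity. The article already concedes that lack of randomisation limits conclusions on efficacy.

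**Conclusion.** The concern holds as a weakness in a stated but provisional list. Matching on the named variables can leave the arms different on baseline SDMT and on pre-baseline MRI activity, and the named diagnostic would not reveal it. The MRI gap is the firmer of the two, because it follows from the stated entry criteria.

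The size is not known. The range of under 1 to about 6 points rests wholly on assumed imbalances (0.2 to 0.5 SD) and assumed odds ratios (1.3 to 2.0 per SD), and the sign follows whichever arm is assumed worse at baseline. It would go too far to say that residual confounding will appear as a benefit of siponimod: the documents give neither the direction of imbalance nor its link to progression. The primary single-arm estimate, its 3.0% precision and the 1500 patients are untouched. The point concerns the supplementary comparison and should be settled before matching is run.

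**What to change.** 1. Add baseline SDMT and pre-baseline MRI activity (gadolinium-enhancing or new/enlarging T2 lesions: yes, no, not done) to the propensity model.
2. After matching, report the standardised mean difference for each covariate, alongside the score distribution.
3. Adjust the matched outcome analysis for baseline EDSS and SDMT.

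The cost is a few more model terms and one balance table. SDMT and MRI both appear in the abbreviation key of Figure 4, and the article describes the two studies' measures as aligned. The figure itself is not shown, so availability at baseline in EVOLUTION should be confirmed. Some matched pairs may be lost: in the simulation the mean fell from 872 to between 788 and 865.

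There is one real limitation. AMASIA records MRI only where available, and a not-done category does not balance true activity among unscanned patients. Its frequency in each arm should be reported.

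The timed 25-foot walk is a tempting further covariate, since in AMASIA "Functional tests comprise the SDMT [36], timed 25-foot walk [52,53], and the nine-hole peg test". It is absent from the Figure 4 key and should not be added unless EVOLUTION is confirmed to collect it.

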## Results

The study will last from February 2020 through February 2025, with an observational phase of 3 years. Recruitment will end after 2 years or after enrollment of 1500 patients, whichever occurs first (Figure 2).

## Discussion

Here, we report the study design of AMASIA, a NIS prospectively including 1500 SPMS patients to be treated with siponimod in the clinical routine of up to 250 German neurological centers. This study will provide first insights on the benefit of siponimod treatment in clinical routine. During the 3-year observational phase, the long-term effectiveness and safety of siponimod will be assessed under real-world conditions, along with data on the quality of life of both patients and caregivers as well as socioeconomic aspects. Overall, the study aims at obtaining a detailed real-world safety and benefit profile of siponimod, complementing both the phase-III study data of EXPAND [29] and the NIS data of PANGAEA 2.0 EVOLUTION [9] (Figure 1).

The primary endpoint of the study is the 6-month confirmed progression of both disability worsening and cognitive decline, as assessed by a novel composite endpoint comprising 6M-CDP in EDSS and SDMT [38]. In clinical trials, EDSS is the most common outcome measure to determine disability progression in MS and a widely used inclusion criterion to define study populations [67]. However, EDSS alone suffers from limited sensitivity, as it is restricted in assessing impairments of upper extremities and cognition, especially at higher scores [68,69]. Since cognition is more severely and more frequently affected in SPMS patients than in RRMS and even primary progressive MS patients [70-72], the SDMT, indexing the most frequently affected information processing speed domain, was chosen as an additional primary outcome measure. In the assessment of information processing speed, SDMT has been proven to be superior to other tests such as the Paced Auditory Serial Addition Test. Moreover, it is simple and requires less time and assessor expertise to complete [73], and several trials have demonstrated its sensitivity in the evaluation of treatment effects [30,74]. Since Kappos et al [38] showed that 6M-CDP, as assessed by either EDSS or SDMT, is of limited sensitivity when compared to the combined 6M-CDP considering both, we decided to employ this novel composite endpoint to increase sensitivity for changes and therapeutic effects of siponimod.

Additional measures aim at completing the picture of siponimod-treated SPMS patients in clinical routine (Figure 3). The clinical disease course will be characterized by MRI, EDSS, and MS activity scale scores. Since EDSS alone does not comprehensively reflect the disability status of patients, long-term effects on disability of lower and upper extremities are determined by the timed 25-foot walk and nine-hole-peg test, respectively. Questionnaires will capture data on symptoms and disease progression, perceived from the perspective of patients, physicians, and relatives. Importantly, the pairwise comparison with data obtained by PANGAEA 2.0 EVOLUTION [8,9] will extend the safety and efficacy profile of siponimod in clinical routine. Comparability is ensured by sample size, population characteristics, length of observational period, visit interval, and test selection (Figure 4). The combination of data obtained by both NIS will extend the efficacy and safety profile of siponimod obtained by the pivotal phase III study EXPAND [29]. In AMASIA, patient selection is less restricted in terms of age and not restricted in terms of comorbidities, EDSS status at baseline, and history of relapses before enrollment. Furthermore, while EXPAND included a much broader SPMS population, AMASIA concentrates completely on the siponimod EMA-label population with active disease. Therefore, AMASIA will better represent the real-world population of siponimod patients with supposedly earlier stages of SPMS.

AMASIA might provide additional mechanistic information on both the anti-inflammatory effects of siponimod (ie, fewer Gd-enhancing lesions and new or enlarging T2 lesions) and the prevention of neurodegeneration. Traditionally, neurodegeneration during MS pathogenesis is considered to be the consequence of inflammatory attacks mediated by the infiltration of leukocytes in the CNS and the release of inflammatory mediators. However, recent publications suggest that inflammation and neurodegeneration might be two separate aspects in progressive MS, with diffuse white matter injury and cortical demyelination on a background of meningeal, perivascular, and parenchymal inflammation [75]. Indeed, preclinical studies indicated that siponimod prevents and attenuates neurodegeneration [22,76] and promotes remyelination of the CNS [23]. While the EXPAND study indicated that patients with ongoing inﬂammatory activity (ie, superimposed relapses in the 2 years before enrollment) benefited most from siponimod treatment [29], a recent subgroup analysis suggested that treatment effects on disability are largely independent from that on relapses because siponimod reduced the risk for confirmed disability progression in both relapsing and nonrelapsing SPMS patients [77]. AMASIA might confirm these findings with long-term data from clinical routine.

As AMASIA is an observational NIS, it might be associated with some limitations. The lack of randomization to siponimod treatment and the heterogeneity of patients in real-life settings might limit robust conclusions regarding efficacy. However, propensity score–matched comparisons of SPMS patients receiving either siponimod (AMASIA) or standard care (PANGAEA 2.0 EVOLUTION) are thought to assess real-world treatment effects and, therefore, complement phase III data on efficacy. Another limitation to be considered is the potential incompleteness of data obtained during visits not following a predefined visit schedule. Obviously, this risk must be assumed to exist, but the intended systematic, standardized data collection, along with regular monitor visits to ensure data integrity, might be sufficient to minimize bias resulting from incomplete data.

In summary, AMASIA will be the first longitudinal study expanding the approval efficacy and safety profile of siponimod with real-world data. Data collected from this study are differentiated from the phase-III study on one hand and from pure registry studies on the other, through the use of the specialized MS management software tool MSDS3D. In particular, the comparison with data obtained from patients of the PANGAEA 2.0 comparator arm EVOLUTION, who are treated according to the current standard of care, will provide even deeper insights into the long-term effectiveness and safety of siponimod as well as its effects on the quality of life and socioeconomic conditions of SPMS patients. After the United States [19], Germany is the second country in which patients have access to commercially available siponimod. Therefore, the results of AMASIA will be particularly helpful for physicians in other countries to expand the long-term efficiency and safety profile of siponimod and to establish a promising treatment option for SPMS patients.

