#### Eligibility of Patients

Treatment initiation with siponimod as routine therapy is at the discretion of the treating physician. The decision for siponimod treatment according to drug label information needs to be made before enrollment and independently of study participation. Participants of all genders are eligible if they are 18 years or older, are diagnosed with SPMS, and provide written informed consent. Patients will be excluded due to off-label therapy, pregnancy and breastfeeding, treatment with siponimod before enrollment, and participation in interventional trials or PANGAEA 2.0 EVOLUTION. Patients who do not attend study visits for more than 12 months will exit the study.

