#### Propensity Score–Matched Comparison With PANGAEA 2.0 EVOLUTION

The real-world evidence study PANGAEA 2.0 [8] has been expanded by the EVOLUTION study arms [9] to clinically characterize SPMS patients and RRMS patients at risk for SPMS. In EVOLUTION, patients aged 18 to 65 years and with moderate to severe disability (EDSS 3.0-6.5) are included if they were previously diagnosed with RRMS and have a current diagnosis of SPMS or RRMS at risk for SPMS. Treatment options at inclusion are current disease-modifying therapies or no treatment during the last 12 months. Any treatment option as well as change of treatment are permitted, thereby representing the standard of care for SPMS prior to availability of siponimod. By having aligned the objectives and measures of EVOLUTION and AMASIA, it will be feasible to compare the demographic and clinical parameters as well as the disease impact on functional domains, cognition, quality of life, and socioeconomic parameters. Since patients in EVOLUTION receive standard of care currently available to these patients, the propensity score–matched comparison with data obtained by AMASIA will provide further insights into the long-term effectiveness and safety of siponimod in clinical practice (Figure 4).

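### Population characteristics do not ensure comparability with EVOLUTION: entry criteria differ on diagnosis, activity, age and EDSS, and the analysis text does not restrict the match to common eligibility

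*Protocol article*

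**What the plan says.** On the comparison with EVOLUTION, the Discussion says: "Comparability is ensured by sample size, population characteristics, length of observational period, visit interval, and test selection". It points to Figure 4, which is not reproduced in the text available.

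**AMASIA.** Eligibility of Patients says: "Participants of all genders are eligible if they are 18 years or older, are diagnosed with SPMS, and provide written informed consent". Off-label therapy is an exclusion. Study Design describes the population as adult SPMS with active disease, shown by relapses or by MRI features, and the Discussion adds that "AMASIA concentrates completely on the siponimod EMA-label population with active disease". Two sentences after the comparability claim, the Discussion describes AMASIA's patient selection as "not restricted in terms of comorbidities, EDSS status at baseline, and history of relapses before enrollment".

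**EVOLUTION.** The section on the propensity score–matched comparison says: "In EVOLUTION, patients aged 18 to 65 years and with moderate to severe disability (EDSS 3.0-6.5) are included". They must previously have been diagnosed with RRMS and must "have a current diagnosis of SPMS or RRMS at risk for SPMS". No disease-activity requirement is stated.

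**Analysis.** Statistical Analysis says that propensity score matching, possibly nearest-neighbor with a caliper, will be used to "compare data from AMASIA with data from the PANGAE 2.0 EVOLUTION arm". It lists six possible variables: age, sex, time since diagnosis, treatment at baseline, relapses in the previous 12 months, and baseline EDSS. The distribution of propensity scores before and after matching will be examined.

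**Intended scope.** The Introduction and the limitations paragraph of the Discussion both describe the matched comparison as one between SPMS patients on siponimod and SPMS patients on standard of care.

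**The concern.** This matched comparison is the only comparative assessment of effectiveness that the article offers, and the limitations paragraph presents it as the answer to the lack of randomization. Its credibility depends on the controls being patients of the same kind. The article treats that as settled by the populations, while the criteria it prints for the two studies differ in four respects.

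Two of the four, diagnosis type and MRI activity, are also missing from the candidate propensity variables. Matching cannot be relied on to balance a characteristic that is neither in the score nor fixed by restriction.

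Both matter on the article's own account. The Introduction characterizes SPMS by irreversibly increasing disability and by cognitive deficits that are more frequent and more severe than in RRMS. These are the two things the EDSS and SDMT components of the primary endpoint measure. On activity, the Discussion reports that patients with superimposed relapses benefited most in EXPAND, and then cites a subgroup analysis suggesting that the effect on disability is largely independent of relapses. Controls without activity could therefore shift the comparison, but the text does not fix the direction.

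**Working it through.** No sample size, power or effect size is stated for the comparison with EVOLUTION, so there is no planned figure to reproduce. The check sets the stated criteria beside the tools meant to align them.

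| Feature | AMASIA | EVOLUTION | In candidate propensity list? |
|---|---|---|---|
| Diagnosis | SPMS | SPMS, or RRMS at risk for SPMS | No (time since diagnosis is a duration, not a type) |
| Activity | Active disease, by relapse or MRI | No requirement stated | Relapses in 12 months: yes. MRI activity: no |
| Age | 18 or older, no upper limit | 18 to 65 | Yes |
| EDSS | No restriction | 3.0 to 6.5 | Yes |

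**Step 1: the claim.** All four rows differ. Population characteristics therefore do not ensure comparability, whatever the matching later achieves.

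**Step 2: age and EDSS.** Both are candidate variables. A caliper on a score containing them would tend to drop AMASIA patients with no close counterpart. It does not guarantee a cut at 65 years or at EDSS 3.0 and 6.5, because the score combines all variables and a difference on one can be offset by another. What remains estimates an effect in the overlap population, not in all siponimod patients.

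**Step 3: activity.** Take an AMASIA patient with no relapse in the past 12 months. To be in AMASIA, this patient should have MRI activity, or a relapse before that window if the label's look-back is longer (the article gives no look-back). An EVOLUTION patient with no relapse in 12 months need have neither. On the listed variables the two can be a good match. Matching on relapse count thus leaves MRI activity unbalanced in the patients whose eligibility rests on it.

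**Step 4: diagnosis.** If the intended SPMS-only scope is applied before matching, diagnosis is dealt with. If the sentence in Statistical Analysis is followed literally, an RRMS patient of similar age, sex, EDSS, relapse count, treatment and disease duration is an acceptable control.

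**Step 5: illustration for RRMS controls (assumed inputs).** Sample Size quotes progression-free rates from EXPAND of 62.2% (siponimod) and 52.3% (placebo), a difference of 62.2 − 52.3 = 9.9 points. Assume that SPMS controls behave like EXPAND placebo, that a share r of the controls is RRMS, and that RRMS controls are progression-free at rate q. Then

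apparent difference = 9.9 − r × (q − 52.3).

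- r = 10%, q = 60%: 9.9 − 0.77 = 9.13 points
- r = 25%, q = 70%: 9.9 − 4.43 = 5.47 points
- r = 50%, q = 80%: 9.9 − 13.85 = −3.95 points

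Neither r nor q is in the article, and the formula ignores any attenuation from matching on EDSS and relapses. The range shows only that the effect of admitting RRMS controls could be anything from negligible to decisive.

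**The case against.** The strongest reply is that the article states the comparison twice as SPMS against SPMS. On that reading diagnosis is a restriction, and nobody would expect it among the propensity covariates, so its absence from the list does not show that RRMS patients enter the match. Statistical Analysis also refers to an EVOLUTION arm in the singular where other sections speak of arms, so its scope is ambiguous. This stands. A reader might infer that the control group will contain RRMS patients and that the comparison is therefore biased against siponimod by a calculable amount. The documents do not support that: the stated intent is the opposite, and both the RRMS share and the RRMS progression rate are unknown.

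Second, age and EDSS are in the list, a caliper is suggested, and the propensity score distribution will be inspected. This also stands. A reader might infer that AMASIA patients outside EVOLUTION's limits spoil the comparison; more probably they are dropped. The consequence is a narrower target population, which the article should state.

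Third, the variable list is headed as possible, the article condenses a fuller protocol, and the limitations paragraph concedes non-randomization and heterogeneity. That excuses missing detail, such as the choice of balance metric. It does not excuse an assertion that the printed criteria contradict: if the covariates are still provisional, comparability is not yet ensured.

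Fourth, the remark that AMASIA is unrestricted in EDSS is made in contrast with EXPAND. It is still a statement about AMASIA, and the eligibility section sets no EDSS limit. Figure 4 may show the differences, but that would not make the sentence in the Discussion correct.

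Finally, the primary endpoint and the sample size rest on single-arm estimation, which this point does not touch.

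**Conclusion.** The point holds in a limited form. The statement that population characteristics ensure comparability with EVOLUTION is contradicted by the criteria printed in the same article, on diagnosis, activity, age and EDSS. The SPMS-only scope is stated as an intention in the Introduction and Discussion but is not carried into the matching section or Statistical Analysis. MRI activity, which with relapses defines the AMASIA population, is handled by neither restriction nor the candidate variables. As written, EVOLUTION patients without active disease can be matched to active-SPMS patients, and RRMS patients possibly can.

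The size of any resulting bias is not established. For RRMS controls, bias against siponimod is plausible if they progress less, but it is conditional on their being admitted. For controls without active disease, even the direction is open. The figures in the working are illustrations on assumed inputs and should not be cited as an estimate. The correction should be made because the comparison carries the article's comparative claims and the repair is cheap; the single-arm primary analysis is unaffected.

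**What to change.** In Statistical Analysis:

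1. State that only EVOLUTION patients with a current SPMS diagnosis enter the match, and analyse the RRMS-at-risk patients separately.
2. Restrict both cohorts to age 18 to 65 and EDSS 3.0 to 6.5 before fitting the propensity model.
3. Restrict to, or match on, disease activity: relapses, and MRI activity where EVOLUTION recorded it, with the same look-back in both studies. If EVOLUTION lacks MRI activity at baseline, say so and name it as a residual difference.
4. Report covariate balance after matching (for example standardized differences) alongside the propensity score distributions.
5. State that the comparative result applies to the overlap population.

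In the Discussion, replace the word ensured with wording that says design and measures were aligned and the populations overlap in part, with comparability to be judged from the balance achieved.

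The cost is fewer matched pairs and a narrower target population. Diagnosis, age and EDSS are entry criteria in EVOLUTION, so items 1 and 2 should need no new data. The activity item is more than a change of wording, because the article does not show whether EVOLUTION recorded MRI activity at entry.
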